**List of abbreviations**

ACE2 Angiotensin converting enzyme2

ALT Alanine transaminase

ARDS Acute respiratory distress syndrome

ASA Acetyl salicylic acid

AST Aspartate transaminase

BARC British academic research consortium

BNP Brain natriuretic peptide

CAD Coronary artery disease

CKD Chronic kidney disease

COPD Chronic obstructive airway disease

COVID -19 Coronavirus disease of 2019

CPAP Continuous positive airway pressure

CPK Creatin phosphokinase

CRP Creactive protein

CVA Cerebrovascular accident

DBP Diastolic blood pressure

DM Diabetes mellitus

HFNC High flow nasal cannula

HIV Human immunodeficiency virus

HPAECs Human pulmonary artery endothelial cells

HTN Hypertension

iNOS Inducible nitric oxide synthase

ITT Intention to treat

LDH Lactate dehydrogenase

LFT Liver function test

NF-Κb Nuclear factor -kb

NO Nitric oxide

NRM Non rebreathing mask

OR Odds ratio

PAD Peripheral arterial disease

PGE2 Prostaglandin E2

PGI2 Prostaglandin I2

PP Per protocol

RAT Rapid antigen test

RFT Renal function test

RNA Ribonucleic acid

RT-PCR Reverse Transcription Polymerase Chain Reaction

SARS-CoV-2 Severe acute respiratory syndrome coronavirus 2

SBP Systolic blood pressure

TGF-β Transforming growth factor -beta

TXA2 Thromboxane A2

ULN Upper limit of normal

VTE Venous thromboembolism

WHO World health organization

**Introduction**

COVID-19 has presented a major threat to public health worldwide. The case fatality rate of COVID-19 is 2%–3%, but the pandemic associated with COVID-19 has been far more severe. SARS-CoV-2 is highly contagious and most individuals within the population are susceptible to infection(1).

SARS-CoV-2 is a single-stranded RNA virus (2). The viral infection is cytopathic to human cells, by binding to membrane-bound angiotensin-converting enzyme 2 (ACE2). ACE2 is expressed abundantly on vascular endothelial cells. The endothelial dysfunction is associated with vasoconstriction, inflammation, permeability, and coagulation(3). The immune-mediated injury may play a critical role in the pathogenesis of COVID-19. In severe forms of COVID-19, the inflammatory cascade may lead to a cytokine storm. The cytokine storm is believed to be a key factor driving both ARDS and extra-pulmonary organ failure (1)

COVID-19 represents a spectrum of clinical manifestations that typically include fever, dry cough, myalgia, weakness, and fatigue, often with pulmonary involvement (1). The majority (81%) of patients had mild manifestations, 14% had severe manifestations, and 5% had critical manifestations. Older adults and those with comorbidities are believed to be at an elevated risk of complications (2). The complications of COVID-19 include pneumonia (75%), acute respiratory distress syndrome (15%), acute liver injury, acute cardiac injury, prothrombotic coagulopathy, acute kidney injury, neurologic manifestations, including impaired consciousness and acute cerebrovascular disease, and shock (4). The disease is associated with lymphopenia, elevated inflammatory markers, and abnormal coagulation parameters(3).

Different treatment modalities might likely have different efficacies at different stages of illness and in different manifestations of the disease. Viral inhibition would be expected to be most effective early in infection, while, in hospitalized patients, immunomodulatory agents may be useful to prevent disease progression and anticoagulants may be useful to prevent thromboembolic complications. Various drugs like antivirals, antibodies, anti-inflammatory agents, targeted immunomodulatory therapies, anticoagulants, and antifibrotics are being evaluated for the management of COVID-19 with limited success so far(4).

The current therapy for COVID-19 involves oxygen support, steroids like dexamethasone, anticoagulation with low molecular weight heparin, and antivirals like remdesivir. However, even with these therapeutic agents mortality is still higher in moderate and severe disease. In patients hospitalized with COVID-19, only dexamethasone has been found to reduce the mortality (5). These therapeutic agents or regimens are not either fully effective or sufficient to combat the complete pathophysiology of the disease.

There is a need for a drug or combination of drugs that can target every component of the pathophysiology of COVID-19. Such therapeutic regimens should be easily available, low cost, and with an established safety profile. There is no single agent which can target all these pathophysiologic substrates. Hence, we aim to evaluate the combination of commonly used cardiac medication (Aspirin, Atorvastatin, and Nicorandil) with anti-inflammatory, antithrombotic, immunomodulatory, and vasodilator properties as adjuvant therapy in covid- 19. Moreover, these drugs are already extensively used, well-tolerated, and having a good safety profile in the human population.

**Review of literature**

**Aspirin**

Aspirin is currently the most widely used drug worldwide since 1897. The benefit of aspirin treatment is now evident for acute coronary syndromes and secondary cardiovascular prevention(6). Aspirin is a typical non-steroidal anti-inflammatory drug with strong anti-inflammatory, anti-thrombotic, and analgesic pharmacological effects. However, prophylactic use of low-dose aspirin is currently controversial in patients with COVID-19(7).

Alveolar capillary micro thrombosis is thought to contribute to the severe lung injury and hypoxemia that occurs in COVID-19 patients. A prior study suggested that systemic anticoagulation reduces mortality in mechanically ventilated COVID-19 patients. In ARDS, aspirin has been studied with mixed results, where some studies have demonstrated benefit and others have not(8).

**Acetylsalicylic Acid as an Anti‑Inflammatory Drug**

ASA exerts its anti-inflammatory effects mostly as a non-selective inhibitor of cyclo-oxygenase (COX-1 and COX-2) enzymes, which are involved in the production of important mediators, including PGs and thromboxane A2 (TXA2). Additionally, ASA can increase acetylation of histone proteins, regulating gene expression. It inhibits virus replication by inhibiting prostaglandin E2 (PGE2) in macrophages and up-regulation of type I interferon production(9).

**Acetylsalicylic Acid as an Anti‑Thrombotic Drug**

Low doses of ASA (e.g., 75–100 mg/day) are sufficient to irreversibly acetylate Ser 530 of COX-1, thus preferentially inhibiting platelet generation of TXA2, a potent vasoconstrictor, and stimulator of platelet reactivity. Reduction of production of PGI2 at higher doses leads to reduced efficacy as antithrombotic. Significant inhibition of platelet activation and aggregation is achieved rapidly by using higher ASA doses ≥ 300 mg followed by lower doses of 75–100 mg daily (10).

Additional mechanisms of ASA-induced effects include down-regulation of inducible nitric oxide synthase (iNOS), oxidative phosphorylation uncoupling, and increased permeability in mitochondria. The pooled results of the Warfarin and Aspirin (WARFASA) and the Aspirin to Prevent Recurrent Venous Thromboembolism (ASPIRE) trials showed that in patients with a first unprovoked venous thromboembolism, ASA reduced the risk of thrombotic event recurrence by 32% (10).

**Acetylsalicylic Acid as an Antiviral Drug**

ASA has significant antiviral activity against several other RNA viruses, including influenza A H1N1 virus, human rhinoviruses, and coxsackievirus subtype A9 (10). Acetylsalicylic acid (ASA), inhibit NF-κB, leading to subsequent inhibition of viral replication (11).

COVID-19 positive Veterans Health Administration patients with active aspirin prescriptions have a significantly decreased risk of mortality as indicated by unadjusted odds ratios of 0.68 (95% CI of0.57–0.80) at 14 days, and 0.68 (95% CI of 0.59–0.77) at 30 days after diagnosis (12).

A retrospective, observational cohort study of adult patients admitted with COVID-19 to multiple hospitals in the United States between March 2020 and July 2020 showed that Aspirin use had a crude association with less mechanical ventilation (35.7% aspirin versus 48.4% non-aspirin, P = .03) and ICU admission (38.8% aspirin versus 51.0% nonaspirin, P = .04), but no crude association with in-hospital mortality (26.5% aspirin versus 23.2% nonaspirin, P = .51). Aspirin use may be associated with improved outcomes in hospitalized COVID- 19 patients(13).

**Potential Role of Acetylsalicylic Acid in COVID‑19**

Aspirin may be useful for the relief of specific symptoms of COVID-19, due to its analgesic and antipyretic effects. it may exert anti-inflammatory, antithrombotic, and antiviral effects, inhibiting the pathophysiological processes leading to the most severe clinical manifestations of COVID-19. Hence, ASA might reasonably be a therapeutic candidate to be tested in COVID-19. Timing of ASA initiation, dosing, duration of treatment, and subgroups of COVID-19 patients that can benefit most from ASA needs to be established.

**Statin**

Statins exert pleiotropic effects on inflammation and oxidative stress, contributing to their beneficial impact on cardiovascular diseases. Statins modulate the immune response at different levels, including immune cell adhesion and migration, antigen presentation, and cytokine production. Statins reduce reactive oxygen species and increasing antioxidants.

Infection with SARS-CoV results in increased induction of the myeloid differentiation primary response 88 (MyD88) gene, which activates the nuclear factor (NF)-kB pathway and induces inflammation. Statins inhibit the MyD88 pathway and tend to preserve MyD88 levels during hypoxia and under stress, which may confer a protective effect in COVID-19 patients (14).

Large observational studies have reported the effectiveness of statin treatment in reducing influenza-related hospitalizations and deaths. An association between outpatient statin use and reduction in disease severity among patients hospitalized during the 2009 H1N1 pandemic has also been demonstrated.

Statins also interfere with ACE2 signaling. After initial entry through ACE2, SARS-CoV-2 down-regulates ACE2 expression, and causing an unopposed angiotensin II accumulation, leading to organ injury. Statins are known to up-regulate ACE2. An increase in ACE2 might prove beneficial for COVID-19 patients (15). A large analysis from an epicentre of the COVID-19 pandemic demonstrated that antecedent statin use was associated with significantly lower rates of in-hospital mortality within 30 days(16).

In this Danish nationwide cohort study, recent statin exposure in patients with COVID-19 infection was not associated with an increased or decreased risk of all-cause mortality or severe infection(17). Statins might mitigate the effects of COVID-19 infection in selected patients based on its associated coagulopathy, endothelial dysfunction, and dysregulated inflammation (18).

A meta-analysis of 9 studies (case series and retrospective cohort studies), with a total of 3449 patients were included in the analysis. The meta-analysis showed that statin use did not improve severity outcome [OR 1.64 (95% CI 0.51e5.23), p ¼ 0.41, I2 ¼ 93%, random-effect modelling] nor mortality rate from COVID-19 infection [OR 0.78 (95% CI 0.50e1.21), p ¼ 0.26, I2 ¼ 0%, fixed-effect modelling]. This study has several limitations. Analysis was limited to retrospective studies only and confounding conditions like comorbidities were not considered (19). Further randomized studies are needed to establish the role of statins in patients with COVID-19.

**Nicorandil**

Nicorandil (N-[2-hydroxyethyl]-nicotinamide nitrate) is a therapeutic agent used clinically for the treatment of angina. Nicorandil acts by increasing nitric oxide (NO) availability and by opening ATP-sensitive K channels (K+ ATP). NO can attenuate the viral receptor (ACE2) interaction through inducing morphological changes in the viral spike (S) protein and may inhibit viral replication through diminishing viral RNA production (20).

**Inflammation and Oxidative stress and modulation by nicorandil**

Nicorandil aborted inflammatory cytokine formation and suppressed apoptosis. Nicorandil inhibits superoxide anion production by the activated neutrophils. The immunomodulatory effect of nicorandil and lung tissue protection against apoptosis is reflected in improved arterial oxygen saturation and oxygen partial pressure. Nicorandil causes bronchodilation and reduces vascular permeability. NO can inhibit the replication cycle of SARS-CoV(20).

Nicorandil can abort the inflammatory process by suppressing monocyte-endothelial adhesion. Nicorandil protected HPAECs from hypoxia-induced apoptosis. Nicorandil has an anti-apoptotic effect through activation of mitoKATP channels and increased eNOS expression, with subsequent inhibition of the NF-κB pathway and the mitochondrial apoptotic pathway(21).

**Anti -fibrotic potential of nicorandil**

The SARS-CoV2 infection has a high tendency for pulmonary parenchymal and interstitial fibrosis(22). The beneficial actions of nicorandil are signaled by a decrease in the profibrotic marker, transforming growth factor-β (TGF-β). Immunohistochemical examination revealed that nicorandil-treated rats exhibited significant diminutions in protein expression levels of transforming growth factor beta-1(TGF-β1) and inducible nitric oxide synthase (iNOS) and enhanced pulmonary protein expression of endothelial NOS (eNOS)(23).

**Anti-Coagulant effect of nicorandil**

NO inhibits platelet activation and limits endothelial-leukocyte adhesion. Nicorandil protected pulmonary endothelium from the thrombus formation and induction of apoptosis, accompanied by both upregulations of endothelial NOS expression and downregulation of cleaved caspase-3 expression(24). Nicorandil prevented sirolimus-induced thrombus formation, presumably due to the reduction of reactive oxygen species (ROS) and endothelial protection(25).

Based on the modulatory role of NO on the interstitial lung thrombo-inflammation, NO can be used as adjuvant therapy. The American Food and Drug Administration (FDA) has recently granted the safety of NO-releasing drugs as supportive therapy in COVID-19 treatment.

**Cardiovascular manifestation in covid-19 and nicorandil**

The involvement of myocardial injury may be linked to the cardiac ACE2 expression. The inflammatory storm caused by SARS-CoV2 infection, respiratory dysfunction, and hypoxemia may be other precipitating factors for the COVID-19 induced cardiac injury. The myocardial dysfunction was described without evidence of obstructive coronary disease. Nicorandil prevents cardiac fibroblast proliferation. The inhibitory effect might be associated with the opening KATP channels, by interfering with the generation of ROS (26). Nicorandil protected cardiac tissues by normalization of cardiac biochemical and oxidative stress parameters and amelioration of histopathological changes(27).

**Nephroprotective effect of nicorandil**

The pathologic hallmark of COVID-19 is proximal tubular injury and loss of brush border due to direct involvement. Other factors mediating acute kidney injury, include systemic hypoxia, coagulopathy, and possible drug nephrotoxicity. Nicorandil administration significantly restored mitochondrial enzymes and oxidative phosphorylation efficacy mediated through enhanced mitoKATP channel function. Based on the various possible benefits of nicorandil therapy in the COVID-19 management, Nicorandil possesses multiple potential modulatory properties on the currently known pathogenesis of the disease(28)**.**

**Method and Materials**

**Objectives**

To test whether triple therapy with aspirin, atorvastatin, and nicorandil is superior to usual care in SARS-CoV-2 infected patients in improving outcome.

To find out the safety of triple therapy in SARS-CoV-2 infected patients.

**Study Design**: Single-centre, prospective, two-arm parallel design, open-label randomized control superiority trial.

**Place of Study**: The study will be conducted at the covid centre of [name] Government Medical College Tanda Kangra, Himachal Pradesh India, converted into a dedicated COVID-19 management centre since August 2020.

**Eligibility criteria**

**Inclusion criteria:**

All SARS-CoV-2 infected patients requiring admission to the study centre will be screened for the trial (figure 1). All patients >18years who are RT-PCR/RAT positive for SARS-CoV-2 infection with pneumonia but without ARDS at presentation (presence of clinical features of dyspnoea hypoxia, fever, cough, spo2 <94% on room air and respiratory rate >24/minute) requiring hospital admission and consenting to participate in the trial will be included.

**Exclusion criteria:**

Patients with documented significant liver disease/dysfunction (AST/ALT > 240), myopathy and rhabdomyolysis (CPK > 5x normal), allergy or intolerance to statins, allergy or intolerance to aspirin, patients taking the following medications: cyclosporine, HIV protease inhibitors, hepatitis C protease inhibitor, telaprevir, fibric acid derivatives (gemfibrozil), niacin, azole antifungals (itraconazole, ketoconazole) clarithromycin, and colchicine, prior statin use (within 30 days), prior aspirin use (within 30 days), history of active GI bleeding in past three months, coagulopathy, thrombocytopenia (Platelet count < 100000/ dl), pregnancy, active breastfeeding, patient unable to take oral or nasogastric medications will be excluded. The patients in altered mental status, shock, acute renal failure, acute coronary syndrome, sepsis, and ARDS at presentation will be excluded.

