**Blinding**

This will be an open-label study. In this study, all participants are aware of participating in the study and enroll in the study after consent. The participants will be aware of the group assigned. Patients receive aspirin, atorvastatin, nicorandil in the intervention group(A) over and above the standard of care, and patients in the control group (B) will receive standard of care only. The health care personal, data collecting officials, and those who evaluate the outcome are aware of the grouping of patients.

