**Intervention groups**

**Intervention group**

Atorvastatin will be prescribed as 40mg starting dose followed by 40 mg oral tablets once daily for ten days or till hospital discharge whichever is later. Aspirin dose will be 325 starting dose followed by 75mg once daily for ten days or till hospital discharge whichever is later. Nicorandil will be given as 10 mg starting dose followed by 5mg twice daily for ten days or till hospital discharge whichever is later. In addition, all patients will receive symptomatic treatment with antipyretics, adequate hydration, anticoagulation with low molecular weight heparin, intravenous remdesivir, corticosteroids (intravenous dexamethasone for 5 days or more duration whenever indicated, if oxygen requirement increasing or inflammatory markers are raised), and oxygen support. Patients will receive treatment for comorbid conditions as per guidelines.

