**Control group**

All patients in the control group will receive symptomatic treatment with antipyretics, adequate hydration, anticoagulation with low molecular weight heparin, intravenous Remdesivir, corticosteroids (intravenous dexamethasone for 5 days or more duration whenever indicated, if oxygen requirement increasing or inflammatory markers are raised), and oxygen support. Patients will receive treatment for comorbid conditions as per guidelines.

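### Exclusion criteria screen for intolerance to and recent use of aspirin and statins but not nicorandil, the third study drug, so a patient with known nicorandil intolerance is eligible

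*Protocol*

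**What the plan says.** The tested regimen has three components. The Protocol's Blinding section states: "Patients receive aspirin, atorvastatin, nicorandil in the intervention group(A) over and above the standard of care". The Intervention group section attaches no condition to the third: "Nicorandil will be given as 10 mg starting dose followed by 5mg twice daily for ten days or till hospital discharge whichever is later".

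The Exclusion criteria set two kinds of screen tied to the study drugs. One is for tolerance: "allergy or intolerance to statins, allergy or intolerance to aspirin". The other is for recent exposure: "prior statin use (within 30 days), prior aspirin use (within 30 days". Nicorandil appears in neither. It is also absent from the list of excluded concomitant medicines, which includes "fibric acid derivatives (gemfibrozil), niacin, azole antifungals (itraconazole, ketoconazole) clarithromycin, and colchicine"; niacin is a different drug.

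The literature review says that nicorandil "is a therapeutic agent used clinically for the treatment of angina". Among cardiac conditions, the exclusions cover acute coronary syndrome at presentation but not stable coronary disease, and the proforma in Appendix-I has a yes/no box for CAD. For controls, the Protocol says: "Patients will receive treatment for comorbid conditions as per guidelines".

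**The concern.** The Protocol treats a tolerance screen and a recent-use screen as necessary for two of its three drugs, then omits both for the third without giving a reason. Eligibility is fixed in a protocol, so a statistical analysis plan could not repair this.

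Two things are at stake. The first is the individual patient: someone with a known intolerance to nicorandil meets the written criteria and may be allocated to it, in a trial whose second objective is the safety of the triple therapy. The second is the contrast: a patient already taking nicorandil may enter as a control and carry one of the three tested drugs into the usual-care arm.

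**Working it through.** The point rests on the text. The Protocol states no figure here that needs reproducing.

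**Step 1. Screens by study drug (Exclusion criteria).**

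| Study drug | Allergy or intolerance | Use within 30 days | Screens present |
| --- | --- | --- | --- |
| Aspirin | yes | yes | 2 of 2 |
| Statin | yes | yes | 2 of 2 |
| Nicorandil | no | no | 0 of 2 |

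**Step 2. Does another section fill the gap?** Inclusion criteria, Randomization, Blinding, Intervention group, Control group, Withdrawal and the proforma contain no nicorandil screen. The exclusions for shock and acute coronary syndrome at presentation concern acute states, not tolerance of or prior exposure to nicorandil.

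**Step 3. Can a current user reach randomisation?** Nicorandil is described as an angina drug, stable coronary disease is not excluded, and nicorandil use is not excluded. A user who has taken neither aspirin nor a statin in the past 30 days is therefore eligible on this point. In the control arm, the sentence on comorbid conditions neither requires nor bars continuing the drug.

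**Step 4. Would the analysis detect it?** The Statistical Analysis section removes from the per-protocol set anyone who receives a treatment other than the assigned one; the intention-to-treat set keeps them. To apply the per-protocol rule, nicorandil use in controls must be known. The Treatment table in Appendix-I has no nicorandil line, and the proforma has no prior-medication section.

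**Step 5. Size of the effect on mortality (illustration).** Inputs from the Sample size section: 20% deaths in controls, 15% under treatment, a difference of 5 points. Assumptions, not in the documents: a fraction f of controls takes nicorandil, and each such patient gains a share w of the full 5-point benefit.

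Diluted difference = (20 − f × w × 5) − 15 = 5 − 5 × f × w points.

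- f = 1%, w = 1/3: 5 − 5 × 0.01 × 0.333 = 4.98 points.
- f = 5%, w = 1: 5 − 5 × 0.05 × 1 = 4.75 points.
- f = 10%, w = 1: 5 − 5 × 0.10 × 1 = 4.5 points.

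Even the last case, in which nicorandil alone delivers the whole benefit, removes only half a point.

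**The case against.** The textual gap is not in dispute. The objections concern what follows from it, and several of them stand.

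- **The asymmetry on prior use may be deliberate.** The literature review reports associations between existing aspirin or statin use and lower COVID-19 mortality, and cites none for nicorandil. Excluding prior users of those two drugs only is a defensible choice. A reader might infer that the 30-day rules exist to keep controls free of all test drugs and every patient new to them. The Protocol gives no purpose for the rules, so that inference is unsupported. This reasoning does not explain the missing intolerance screen.
- **Many users are probably excluded already.** Angina patients on nicorandil would plausibly often take aspirin or a statin too. This is itself an assumption, but a reasonable one. A reader might apply a share of 1% to 5% to the planned 396 and obtain about 4 to 20 enrolled users. The documents give no such share, and the calculation ignores this filter.
- **The objective is not about starting the drug.** A reader might argue that a prior user in the intervention arm defeats the trial's purpose. The stated comparison is triple therapy against usual care; nothing limits it to patients new to nicorandil.
- **A 1-in-2 chance of harm is not shown.** Blocks of four suggest equal allocation, but the ratio is not stated. In any case, one half would be the chance of allocation, not a frequency of intolerance or of reactions. Clinical staff assess eligibility in an open-label trial and may decline such a patient. That would be an unwritten exclusion, so the text still needs correcting.
- **Some of the gap is not specific to nicorandil.** The proforma has no line for prior aspirin or statin use either. The sentence on comorbid conditions could also allow controls to start aspirin or a statin, so a nicorandil criterion alone would not guarantee a control arm free of the study drugs.

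**Conclusion.** The point holds in two parts of unequal weight. The main part is that a patient with known nicorandil intolerance is eligible for randomisation to a regimen containing it, while the same patient would be excluded if the intolerance were to aspirin or a statin. This follows from the text alone and is a matter of patient safety; how often it would arise cannot be derived from the documents.

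The secondary part is that a current nicorandil user can enter either arm, and nothing bars the drug in controls. The number of such patients is unknown and probably reduced by the existing exclusions. Under the assumed range of 1% to 10% of controls, the planned 5-point difference falls to between 4.98 and 4.5 points. The omission therefore does not threaten the primary comparison, but it should be corrected because the remedy is simple and the safety gap is plain.

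**What to change.** Reconcile the Exclusion criteria with the Blinding, Intervention group and Control group sections so that all three study drugs are screened consistently, at least for known allergy or intolerance, or state why nicorandil is treated differently. Whether a recent-use rule should also cover nicorandil, and in what terms, is for the sponsor to decide and explain.

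Add nicorandil history and in-hospital use to the Appendix-I proforma, so that exposure in controls can be identified when the per-protocol set is formed. The same form change could cover aspirin and statins, which also lack a line.

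The cost is a line in the eligibility text, a screening question and a few proforma fields. The downside is the loss of a few otherwise eligible patients.

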**Investigation**

Baseline investigations like complete blood count, liver function test, renal function test, fasting blood sugar, LDH, D-dimer, CRP, serum ferritin, BNP, Trop-I, CPK, PT/INR, procalcitonin - will be done at admission. RFT, LFT, CPK, Trop-I, BNP, D-dimer, CRP, serum ferritin will be repeated on the 5^th^ day and at the time of discharge.

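### The exclusion criteria bar a recent bleed only if it was gastrointestinal and name no anticoagulant or non-aspirin antiplatelet, so some patients at raised bleeding risk can be allocated to study aspirin on top of heparin

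*Protocol*

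**What the plan says.** The Exclusion criteria section of the Protocol deals with bleeding risk through a short set of items: allergy or intolerance to aspirin, "history of active GI bleeding in past three months, coagulopathy, thrombocytopenia", and recent use of two of the study drugs, "prior statin use (within 30 days), prior aspirin use (within 30 days". Coagulopathy carries no definition or threshold. A separate list of barred medicines runs from cyclosporine and protease inhibitors to azole antifungals and colchicine; it holds no anticoagulant and no antiplatelet. The section ends with acute states: "The patients in altered mental status, shock, acute renal failure, acute coronary syndrome, sepsis, and ARDS at presentation will be excluded".

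The Investigation section adds clotting tests at baseline: "PT/INR, procalcitonin - will be done at admission".

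The Intervention group section then assigns aspirin: "Aspirin dose will be 325 starting dose followed by 75mg once daily for ten days or till hospital discharge whichever is later". Both arms receive heparin. The Intervention group section has "anticoagulation with low molecular weight heparin, intravenous remdesivir" and the Control group section has "anticoagulation with low molecular weight heparin, intravenous Remdesivir". Both sections also say that comorbid conditions are treated according to guidelines.

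**The concern.** The authors accept that a recent bleed is a reason to withhold study aspirin, but apply this to one site only. They also screen concomitant medicines by name, yet name none that adds to aspirin's effect on bleeding. A site that follows the written list would turn away a patient with a recent gut bleed and admit one with a recent intracranial bleed.

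What is at stake is the safety of the individual patient. The review of aspirin in the Protocol itself states: "Significant inhibition of platelet activation and aggregation is achieved rapidly by using higher ASA doses", the doses meant being 300 mg or more, followed by 75 to 100 mg daily. That matches the regimen assigned here, if the starting dose of 325 is in mg. Heparin is common to both arms, so the aspirin is what allocation adds for such a patient (leaving aside any antiplatelet action of nicorandil, which the Protocol also describes). Safety is one of the two stated objectives of the trial.

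**Working it through.** No arithmetic applies. The check is to run example patients through the written criteria, assuming each meets the inclusion criteria and has no other exclusion.

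| Patient | Rule that applies | Outcome as written |
|---|---|---|
| Active gastrointestinal bleed six weeks ago | Three-month gastrointestinal bleeding rule | Excluded |
| Intracranial bleed six weeks ago, now alert and stable, normal platelets and clotting | None | Eligible |
| Other major non-gastrointestinal bleed six weeks ago, now stable | None | Eligible |
| P2Y12 inhibitor plus aspirin | Aspirin within 30 days | Excluded |
| P2Y12 inhibitor alone, no aspirin or statin for 30 days | None | Eligible |
| Warfarin with a raised INR | Coagulopathy, if the clinician reads it so | Uncertain |
| Direct oral anticoagulant, no aspirin or statin for 30 days | Coagulopathy, only if the clinician counts the drug itself | Uncertain, and eligible on a plain reading |

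Next, whether other rules close the gap:

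- **Coagulopathy with the admission PT/INR.** With no threshold, the reader decides whether a drug effect counts. PT/INR does not measure platelet function, so it cannot reveal a P2Y12 inhibitor. That it is also an unreliable sign of a direct oral anticoagulant is general laboratory knowledge, not something the Protocol states; the antiplatelet and prior-bleed cases do not depend on it.
- **Altered mental status and shock.** These apply at presentation. They may catch an acute intracranial or haemorrhagic event, but not a recent one in a patient who has recovered.
- **The 30-day aspirin and statin rules.** These remove many patients with vascular disease, but not someone who takes only an anticoagulant or only a non-aspirin antiplatelet.
- **Diagnosis.** The comorbidity table in Appendix-I lists venous thromboembolism, valvular heart disease, stroke and peripheral arterial disease, and the Exclusion criteria bar none of them. This is weak evidence, because the table is a general checklist and also lists chronic liver disease, although significant liver disease is an exclusion. It does not show how many patients take such drugs.

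Last, what happens after entry. The treatment table in Appendix-I has a row for low molecular weight heparin but none for oral anticoagulants or other antiplatelets, so the form would not prompt anyone to notice a combination. Bleeding is a safety endpoint observed in hospital (Safety endpoints), with telephone evaluation after discharge to day ten (Follow-up). These steps record harm after it occurs. The Protocol contains no rule on other antithrombotic drugs during study treatment.

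**The case against.** The strongest objection concerns the anticoagulant group. A reader might infer that every patient on a home anticoagulant would receive that drug, heparin and aspirin together. The Protocol does not say so. It names heparin as the anticoagulation for all patients, and if heparin replaces the home drug, the patient has the same combination as everyone else in the intervention arm. This stands, and it is why the point is limited to a drug that will continue during study treatment. The Protocol does not require replacement either, and its instruction to treat comorbid conditions by guideline leaves continuation open. Replacement by heparin does not answer the antiplatelet case, since heparin is not an antiplatelet, nor the prior-bleed case.

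A reader might also infer that eligibility is the only place to control this risk. It is not: a rule on concomitant antithrombotics during treatment could do part of the work. No such rule is present, and it would not address a recent bleed.

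Nor should the assigned aspirin dose be read as a measure of added harm. The regimen is the same for every intervention patient, some will die or stop early and receive less, and the Protocol gives no bleeding risk for the combinations in question.

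Finally, the trial is open-label and the treating team knows who receives aspirin, so clinicians may decline such patients by judgement. That makes an inadvertent combination less likely than under blinding, but it is not a written safeguard. The Randomization section gives eligibility to the person admitting the patient, and the Exclusion criteria contain no clause for investigator discretion. It is also fair to say that the existing rules narrow the group considerably.

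**Conclusion.** The gap is real and should be closed. As written, the Exclusion criteria admit an alert, stable patient with a recent intracranial or other major non-gastrointestinal bleed, and a patient whose oral anticoagulant or non-aspirin antiplatelet continues during study treatment; either can be allocated to aspirin on top of heparin. This is more than missing detail, because the stated rule treats two recent major bleeds differently by site alone, and eligibility belongs in the protocol rather than in a statistical analysis plan.

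The number affected is not given and is probably small, given the aspirin, statin and acute-state exclusions. The size of the added bleeding risk cannot be derived from the Protocol. The conclusion rests on two assumptions: that coagulopathy is not routinely read to include any antithrombotic drug, and, for the drug-related group, that the home drug is continued. A reader might infer a threat to the comparison of the arms; the Protocol gives no ground for that, because the same criteria apply before allocation to both arms, and no effect on bias, power or error rates is claimed.

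**What to change.** Add one sentence to the Exclusion criteria: intracranial or other major bleeding at any site in the past three months, or current oral anticoagulant or non-aspirin antiplatelet (for example P2Y12 inhibitor) treatment that will continue during study treatment. The person assessing eligibility checks both before randomisation. The three-month window follows the existing gastrointestinal rule; whether any lifetime intracranial haemorrhage should also exclude is a clinical decision for the investigator.

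The cost is a short amendment, two screening questions at admission and slightly fewer eligible patients, a number that the Protocol does not allow one to estimate.
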